### 2.8. Outcomes

Study outcomes are designed to quantify the comparative effects of functional low-GI foods versus conventional wholegrain foods on glycolipid metabolism and selected vascular biomarkers within a randomized crossover design. Endpoints will be assessed at prespecified trial visits, and analyses will account for treatment, period, and within-participant effects, in accordance with the statistical approach outlined in the protocol.

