### 2.9. Assessments

#### 2.9.1. Laboratory Procedures

At Day −28 and at each subsequent visit, fasting blood samples will be collected to measure fasting plasma glucose, TG, total cholesterol, HDL-C, non-HDL-C, low-density lipoprotein cholesterol (LDL-C), very-low-density lipoprotein cholesterol (VLDL-C), apolipoprotein B100 (ApoB100), apolipoprotein AI (ApoAI), liver enzymes (aspartate aminotransferase (GOT), alanine aminotransferase (GPT), and gamma-glutamyl transferase (gamma-GT)), creatinine, and uric acid [10,11]. All assessments requiring fasting blood sampling will be scheduled in the morning following an overnight fast of at least 12 h; participants will be instructed not to consume any food or caloric beverages (including the study products) before the visit (water allowed). Whenever feasible, visits will be planned at a similar time of day across study periods to minimize diurnal variability. The TyG index will be calculated using the formula ln[fasting TG (mg/dL) × fasting glucose (mg/dL)/2] [9]. Samples will be processed according to standardized laboratory procedures: plasma will be separated by centrifugation shortly after collection, aliquoted into pre-labeled cryovials using coded identifiers to minimize freeze–thaw cycles, and stored in monitored −80 °C freezers with restricted access. Batched measurements will be prioritized when applicable to reduce inter-assay variability. Future ancillary analyses will be limited to cardiometabolic and inflammatory biomarkers consistent with the study objectives and will be conducted in accordance with ethics approval and applicable data protection regulations.

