### 2.12. Statistical Analysis Plan

Analyses will be performed using IBM SPSS Statistics (version 28.0). Continuous variables will be summarized as mean (SD) or median (interquartile range (IQR)), as appropriate, and categorical variables as counts and percentages. Treatment effects will be estimated within the crossover framework using linear mixed-effects models, including treatment, period, and sequence as fixed effects, and participant (nested within sequence) as a random effect to account for within-participant correlation. Accordingly, for the primary endpoint, the treatment effect will be interpreted as the between-intervention difference in period-specific change in TyG. Potential carryover effects will be explored by adding a treatment-by-period interaction term and by comparing period-specific baseline values; if evidence of carryover is observed, sensitivity analyses will be conducted, including analyses restricted to first-period data. Model assumptions (normality of residuals and homoscedasticity) will be assessed; when violated, data transformation and/or non-parametric sensitivity analyses (e.g., Wilcoxon signed-rank test for paired comparisons) will be considered, with paired estimates reported as supportive analyses. A per-protocol analysis will be performed excluding participants with major protocol deviations. Extreme values will be evaluated using the pre-specified approach, including Dixon’s Q test where applicable. All tests will be two-sided, with α = 0.05.

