Nevertheless, several limitations should be considered. As a single-center pilot trial, findings will primarily inform feasibility, directionality, and effect-size estimation rather than definitive clinical efficacy. Each intervention period lasts 28 days and the protocol relies on surrogate metabolic and vascular biomarkers rather than hard clinical outcomes; accordingly, any observed improvements should be interpreted as short-term biomarker modulation and proof-of-concept evidence, not as durable cardiometabolic risk reduction. Carryover and period effects remain intrinsic to crossover designs, and the planned evaluation of carryover signals and sensitivity analyses restricted to first-period data will be important for preserving interpretability if such effects emerge. Blinding may be challenged by sensory differences between products, and residual variability in background diet may persist despite counseling and stabilization measures. Endothelial reactivity will be assessed using the Endocheck^®^/Vicorder^®^ system; while practical and standardizable for a double-blind intervention setting, this approach is less extensively validated than ultrasound-based FMD and does not have a well-established minimal clinically important difference; therefore, vascular findings will be interpreted primarily using effect sizes and confidence intervals. Moreover, eligibility is restricted to adults with BMI ≤ 30 Kg/m^2^; thus, generalizability to individuals with obesity or more advanced metabolic impairment may be limited. Because the functional and control products differ in fiber, protein, and labeled carbohydrate content, any observed effects will reflect the combined influence of the overall nutritional matrix and carbohydrate quality, and cannot be attributed to glycemic index alone.

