## Figures and Tables

**Figure 1 jcm-15-01745-f001:**
[figure not shown]
CONSORT-style flow diagram of the GLOW randomized, double-blind crossover trial.

**Table 1 jcm-15-01745-t001:** Eligibility criteria.

Section	Criteria
Inclusion criteria	(1) Male or female aged ≥18 years (2) Fasting TG > 150 mg/dL (3) Ability to communicate and comply with study requirements (4) Written informed consent provided
Exclusion criteria	(1) Gluten hypersensitivity/coeliac disease diagnosis (2) BMI > 30 kg/m^2^ (3) Preventive treatments (e.g., lipid-lowering drugs, antihypertensives) not stabilized in type and dose for ≥3 months (4) Any medical or surgical condition limiting adherence to the protocol

BMI, Body mass index; TG, Triglycerides.

**Table 2 jcm-15-01745-t002:** Nutritional composition of the study carbohydrate products (as provided by product labeling).

Nutrients	Functional Low-GI Products (Altograno^®^ Flour)	Control Products (Standard Wholegrain Flour)
Energy (kJ/kcal)	1413/335	1481/350
Fat (g)	2.5	2.0
Saturates (g)	0.7	0.4
Carbohydrates (g)	53	66
Sugars (g)	4.1	3.0
Fiber (g)	12.0	8.0
Protein (g)	19	13
Salt (g)	0	<0.01

Low-GI, low glycemic index.

**Table 3 jcm-15-01745-t003:** SPIRIT Schedule of Enrolment, Interventions, and Assessments for the GLOW Trial.

Procedures/Assessments	Enrolment (Day −28)	Allocation/Baseline (Day 0)	End of Period 1 (Day 28)	Start of Period 2 (Day 56)	End of Study (Day 84)
Informed consent	X	X			
Eligibility assessment	X	X			
Medical history	X				
Randomization/allocation		X			
Nutritional visit + dietary counseling	X	X	X	X	X
Anthropometrics	X	X			
Hemodynamic tests (BP, HR)	X	X	X	X	X
Blood chemistry (fasting)	X	X	X	X	X
Endothelial function		X	X	X	X
Study food dispense		X		X	
Study food intake (daily)		X	X		
Return of uneaten food			X	X	X
Washout (no study foods)			X	X	
Acceptability evaluation			X		X
Adverse events assessment	X	X	X	X	X

BP, blood pressure; HR, heart rate.

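### The signed-rank test and paired estimates named as fallback in Section 2.12 have no period term, although the plan says its analyses account for period

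*Protocol article*

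**What the plan says.** Section 2.8 (Outcomes) of the protocol article states that "analyses will account for treatment, period, and within-participant effects". Section 2.12 carries this into the main model, "including treatment, period, and sequence as fixed effects, and participant (nested within sequence) as a random effect". The Discussion adds that "Carryover and period effects remain intrinsic to crossover designs".

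For the case where normality or constant variance fails, Section 2.12 offers data transformation and/or a non-parametric sensitivity analysis. The single example is the "Wilcoxon signed-rank test for paired comparisons) will be considered, with paired estimates reported as supportive analyses". No period adjustment is mentioned for either the test or the paired estimates.

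The same section says that "Extreme values will be evaluated using the pre-specified approach, including Dixon’s Q test where applicable". It does not name the variable tested or say what happens to a flagged value.

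**The concern.** In a two-period crossover, the difference functional minus control contains the period difference with a plus sign in one sequence and a minus sign in the other. A signed-rank test pools these differences. With equal sequences the period difference averages out of the estimate but stays in the spread, so the test loses power. With unequal sequences it also moves the estimate.

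The fallback would be used when the residuals look poor, most plausibly for skewed secondary variables such as raw triglycerides or hsCRP. Section 2.11 says secondary endpoints will be read mainly through effect sizes and confidence intervals, so a shifted or needlessly wide paired estimate would affect what is reported.

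Some period effect in the change score is plausible. Table 3 marks eligibility at Day −28 and again at Day 0, and Day 0 is also the Period 1 baseline, whereas the Period 2 baseline (Day 56) plays no part in selection. Dietary counselling is repeated at every visit.

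**Working it through.** **The plan's own figure.** Section 2.11 gives two-sided alpha 0.05, 80% power, SD 0.7, 33 participants required, 40 enrolled and a detectable difference of about 0.30–0.35. Reading 0.7 as the SD of the paired difference, n = (0.7 × (1.960 + 0.842) / 0.35)² = 31.4. That rounds up to 32, or 34 with the t distribution, so 33 is reproduced to within two. At n = 40 the detectable difference is 0.7 × 2.802 / √40 = 0.31. The checks below use SD 0.7, effect 0.35 and 34 completers (40 less 15%).

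**Formulae.** Let τ be the treatment effect and π the period shift (Period 1 minus Period 2 response).
- Functional minus control has mean τ + π in the functional-first sequence and τ − π in the control-first sequence.
- The pooled paired mean is τ + π × (n1 − n2)/(n1 + n2).
- With n1 = n2 the pooled SD is √(SD² + π²).
- Period 1 minus Period 2 has mean π + τ in one sequence and π − τ in the other. The between-sequence shift is therefore 2τ and π cancels, which is why half the shift estimates τ.

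The documents give no value for π. It is assumed over a range.

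**Equal sequences, 17+17 (8,000 simulated trials per setting).**

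| Assumed π | Pooled SD | Signed-rank power | Rank-sum power | Signed-rank type I error |
|---|---|---|---|---|
| 0 | 0.700 | 79% | 79% | 4.7% |
| 0.10 | 0.707 | 79% | 78% | 4.3% |
| 0.20 | 0.728 | 76% | 78–79% | 4.0% |
| 0.35 | 0.783 | 70% | 78% | 2.8% |
| 0.50 | 0.860 | 61% | 79% | 1.6% |

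The rank-sum test compares Period 1 minus Period 2 differences between sequences. Its type I error stays near 5% throughout. A separate run at 17/16 with effect 0.341 agrees: signed-rank power is 75.6%, 74.7% and 69.7% at shifts of 0, 0.20 and 0.35, against about 75% for the rank-sum at each.

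**Unequal sequences, 20/14.** Bias is π × 6/34: 0.018 at π = 0.10, 0.035 at 0.20 and 0.062 at 0.35 TyG units. The article states 1:1 allocation without mentioning blocks. If allocation were simple (an assumption), 40 participants would split with a gap of 6 or more with probability 0.43, before any dropout or per-protocol exclusion.

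**Dependence on the SD.** The loss of power and size depends on π/SD. If the paired-difference SD were 0.35, a shift of 0.175 would do what 0.35 does at SD 0.7. A shift of 0.35 would cut the signed-rank type I error to about 0.5%.

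**Dixon's Q.** Eligibility is "Fasting TG > 150 mg/dL" (Table 1). The primary variable is already logarithmic: "The TyG index will be calculated using the formula ln[fasting TG (mg/dL) × fasting glucose (mg/dL)/2". Assume ln TG normal with median 110–180 mg/dL and SD 0.4–0.5, cut at 150, with visit noise of 0 or 0.20 on ln TG (0.20 for changes) and glucose log-SD 0.10. At n = 40 and a nominal 5%, the test flags a value with no error present in:
- raw TG levels: 26–35% of samples
- raw TG changes: 20–21%
- TyG levels: 6–13%
- TyG changes: about 5%

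A lognormal with no cut at 150 and log-SD 0.3–0.5 already gives 16–27% for raw TG.

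**The case against.** The main analysis adjusts for period and so meets the Section 2.8 commitment. The signed-rank test is reached only if assumptions fail. Even then it is one example, listed after transformation, and only to be considered; the paired estimates are labelled supportive. All of this stands, and it limits the consequence. It does not remove the point, because the article chose to name a method and that method omits period.

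A second objection is that large period shifts are not shown to be likely. A shift of 0.35 equals the top of the effect range the trial aims to detect. With an assumed TG median of 115, log-SD 0.5 and within-person log-SD 0.15–0.30, selection at Day −28 alone gives an expected Day 0 to Day 28 shift of zero. Requiring TG above 150 at both Day −28 and Day 0 gives 0.03–0.14. At SD 0.7 such shifts cost little. This stands too. The larger losses need either another source of period effect or a paired-difference SD well below 0.7. The latter is possible, since Section 2.11 takes 0.7 from population datasets.

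On outliers, a reader might infer that Dixon's Q will strip out genuine high-triglyceride responses because the sample is cut at 150 mg/dL. The article does not support this. It says extreme values are evaluated, where applicable, and never that they are removed. The primary endpoint, change in TyG, is flagged at the nominal rate. The excess for raw TG comes largely from ordinary skewness, not from the entry threshold.

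**Conclusion.** The point holds for the fallback and supportive analyses only. The named signed-rank test and paired estimates omit the period effect that Section 2.8 says is accounted for.

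It would be wrong to conclude that the primary result is compromised, because the mixed model keeps period. It would also be wrong to conclude that the fallback is generally biased: with equal sequences it is unbiased and conservative. At SD 0.7 and 17+17 the power loss is negligible for a shift of 0.10 or less, about 3 percentage points at 0.20 and 8 at 0.35. Bias arises only with unequal completers and at 20/14 is 0.02 to 0.06 TyG units for shifts of 0.10 to 0.35. All of these rest on an assumed period shift and on reading 0.7 as the SD of the paired difference.

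On Dixon's Q only a minor note remains: it assumes normality and over-flags right-skewed variables such as raw TG, but not change in TyG.

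**What to change.** In Section 2.12, replace the signed-rank example with the Wilcoxon rank-sum test comparing within-participant Period 1 minus Period 2 differences between the two sequences. Report half the Hodges-Lehmann shift, with its confidence interval halved likewise, as the treatment estimate. State that any supportive paired estimate is period-adjusted, for example as half the difference between the two sequence means of those period differences.

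As a clarification, say which variable and scale Dixon's Q is applied to, and that a statistical flag alone does not remove a value.

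The cost is wording. The data do not change and both procedures are standard. With no period effect the power loss is negligible: 75.6% against 74.9% at 17/16, and no visible difference at 17+17.

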### 2.13. Data Management and Confidentiality

All data will be recorded in study-specific paper and electronic case report forms (CRFs) approved by the Ethics Board and managed through the Research Electronic Data Capture (REDCap)-Unibo platform. All information will be handled as strictly confidential in accordance with Good Clinical Practice (GCP) standards and applicable data protection regulations [17], including the General Data Protection Regulation (GDPR; EU 2016/679) [18]. Data will be stored securely using coded identifiers, restricted access procedures, and protected systems. Any data security breach will be promptly contained, with appropriate impact assessment, required notifications, and corrective actions implemented to prevent recurrence.

### 2.14. Ethics, Insurance, Funding, and Dissemination

The study will be conducted in accordance with International Council for Harmonization (ICH)-GCP, the Declaration of Helsinki (2013) [19], and applicable European and local regulations. The trial will commence only after ethics committee approval and the required institutional authorizations have been obtained, including approval from the IRCCS General Director, and after confirmation of appropriate study-specific insurance coverage. The study is a non-profit initiative sponsored by the University of Bologna (Department of Medical and Surgical Sciences (DIMEC)) and supported by funds allocated to the Principal Investigator under the National Recovery and Resilience Plan (NRRP) “ON Foods” project framework. Results will be disseminated through scientific meetings and peer-reviewed publications, irrespective of study outcomes.

## 3. Discussion

This exploratory, randomized, double-blind, controlled crossover trial is designed to test whether substituting commonly consumed cereal-based staples with functional low-glycemic index alternatives can produce measurable short-term improvements in an integrated marker of insulin resistance-related glycolipid dysregulation, the TyG index, in adults with fasting TG >150 mg/dL. By combining a pragmatic dietary substitution model with a within-participant comparison framework, the study aims to generate proof-of-concept evidence on the metabolic responsiveness of a clinically relevant phenotype characterized by suboptimal triglyceridemia but otherwise preserved health status.

A key strength of the protocol is the selection of TyG as the primary endpoint, given its simplicity, accessibility, and clinical relevance as a surrogate marker of insulin resistance in preventive cardiometabolic medicine [2]. Prospective cohort data support the prognostic value of TyG for incident cardiovascular disease and mortality outcomes, reinforcing its suitability as a clinically meaningful surrogate endpoint in dietary intervention studies [3,4]. In addition, TyG has been associated with vascular aging phenotypes, including arterial stiffness, and with long-term adverse cardiometabolic outcomes, such as incident diabetes, coronary events, stroke, and cardiovascular mortality, further supporting its translational relevance beyond metabolic risk stratification alone [20]. Notably, evidence comparing insulin resistance surrogates suggests that TyG may be a better predictor of cardiovascular risk than the homeostasis model assessment of insulin resistance (HOMA-IR), strengthening the rationale for prioritizing TyG as a primary outcome in cardiometabolic prevention research [21].

The intervention is intentionally designed as a pragmatic “food substitution” strategy, whereby participants replace habitual pasta- and bread-based staples with predefined study products within a stabilized dietary background, thus aiming to minimize behavioral burden and improve real-world applicability [6]. This design choice is relevant because carbohydrate quality—rather than total carbohydrate intake alone—appears to influence intermediate cardiometabolic traits, including TG and TyG-related profiles [6]. Consistent with this concept, intervention evidence in individuals with metabolic syndrome has shown that a whole-grain cereal-based diet (compared with refined cereals) reduces post-prandial insulin and triglyceride responses over 12 weeks, supporting the biological plausibility that cereal quality can modulate dynamic glyco-lipid handling [7]. Furthermore, dietary patterns characterized by adverse glyco-lipid signatures have been associated with higher odds of type 2 diabetes, with TyG contributing as an intermediary marker in the pathway linking dietary exposures and dysglycemia-related outcomes. Together, these observations reinforce the rationale for targeting diet-induced glycolipid dysregulation through feasible, product-level dietary modifications [22].

Mechanistically, the expected direction of effect is likely mediated predominantly through post-prandial pathways, as attenuating glycemic excursions can influence insulin dynamics and downstream hepatic lipid handling, with potential implications for triglyceride-rich lipoprotein metabolism [7]. This is particularly relevant in participants with fasting TG >150 mg/dL, a phenotype in which exaggerated post-prandial lipemia and impaired metabolic flexibility may coexist even in the absence of overt disease [6]. Experimental data also supports a link between refined carbohydrate exposure and early metabolic impairment accompanied by endothelial alterations, including increases in TyG and reduced vascular reactivity in preclinical models, providing additional mechanistic coherence to the hypothesis that carbohydrate quality may influence both metabolic and vascular physiology [23].

In this context, the inclusion of endothelial function assessment provides an additional translational layer by integrating metabolic endpoints with vascular responsiveness [20]. Although the present protocol assesses endothelial reactivity rather than arterial stiffness directly, convergent human evidence supports diet–vascular relationships along the same cardiometabolic axis, including observations that greater adherence to a Mediterranean dietary pattern is associated with lower vascular stiffness parameters across broad community-based samples stratified by insulin resistance status defined through TyG [24]. This alignment supports the clinical plausibility that metabolic improvements captured by TyG may coincide with more favorable vascular function metrics, even over relatively short intervention windows [24].

Beyond the primary endpoint, the secondary biomarker panel (including non–high-density lipoprotein cholesterol and apolipoprotein B) is clinically informative because it may clarify whether any observed metabolic changes translate into broader improvements in atherogenic lipoprotein burden [3]. This is particularly relevant given that TyG-related indices have been linked to more advanced coronary phenotypes when combined with anthropometric parameters, and diet-related insulin load constructs have been associated with greater coronary artery disease severity in at-risk clinical cohorts, suggesting an overarching pathway connecting diet, insulin resistance surrogates, and vascular disease progression [25]. In addition, measuring hsCRP may help contextualize metabolic findings within systemic inflammatory status, which often co-varies with insulin resistance surrogates and cardiometabolic risk profiles [21].

Several methodological strengths enhance the internal validity of this protocol. The randomized crossover design enables within-participant comparisons, improving efficiency and reducing confounding by stable inter-individual characteristics, which is particularly valuable in a pilot setting [6]. The double-blind approach further reduces expectancy effects and performance bias, which can be challenging to control in food-based interventions [7]. Product accountability and structured adherence assessment add robustness by supporting exposure standardization and interpretability of treatment contrasts [6].

Nevertheless, several limitations should be considered. As a single-center pilot trial, findings will primarily inform feasibility, directionality, and effect-size estimation rather than definitive clinical efficacy. Each intervention period lasts 28 days and the protocol relies on surrogate metabolic and vascular biomarkers rather than hard clinical outcomes; accordingly, any observed improvements should be interpreted as short-term biomarker modulation and proof-of-concept evidence, not as durable cardiometabolic risk reduction. Carryover and period effects remain intrinsic to crossover designs, and the planned evaluation of carryover signals and sensitivity analyses restricted to first-period data will be important for preserving interpretability if such effects emerge. Blinding may be challenged by sensory differences between products, and residual variability in background diet may persist despite counseling and stabilization measures. Endothelial reactivity will be assessed using the Endocheck^®^/Vicorder^®^ system; while practical and standardizable for a double-blind intervention setting, this approach is less extensively validated than ultrasound-based FMD and does not have a well-established minimal clinically important difference; therefore, vascular findings will be interpreted primarily using effect sizes and confidence intervals. Moreover, eligibility is restricted to adults with BMI ≤ 30 Kg/m^2^; thus, generalizability to individuals with obesity or more advanced metabolic impairment may be limited. Because the functional and control products differ in fiber, protein, and labeled carbohydrate content, any observed effects will reflect the combined influence of the overall nutritional matrix and carbohydrate quality, and cannot be attributed to glycemic index alone.

